### Recruitment and retention

Eligible adolescents will be recruited by the study personnel in the trial site (e.g. trial physician or nurse). Each study participant will be assigned to a study nurse working in the HIV treatment hospital and they will be tracked with their mobile phone numbers.

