### Trial sites selection

Twelve hospitals in Anambra State that offer HIV services will be randomly selected from all the hospitals in the state that provide HIV services. The hospitals included are registered by the National Agency for the Control of AIDS (NACA) to offer HIV services. The hospitals (the clusters) will be matched by type of hospital (e.g. secondary or tertiary) and the paired units will be randomly assigned to intervention or control.

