### Participants

Eligibility criteria for participants will include the following: all patients with HIV who had transitioned from pediatric stage to a young person/adult; 10–19 years irrespective of CD4+ cell count; initiated into HIV care and antiretroviral therapy for minimum of 6 months; currently off ART despite multiple attempts to restart; poor medication adherence (< 95% adherence rate assessed through pill count or self-report); willing to restart therapy and sign a written informed consent (see Additional file 2).

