### Intervention

A structured adherence support scheme termed the ‘Incentive Scheme’ will be applied to the intervention hospitals while the control hospitals will receive usual care. The Incentive Scheme added to the usual care involves financial incentives linked to viral load (VL) combined with attendance for motivational interviewing (MI) with an adherence counsellor trained in MI techniques. (Table 2) [14]. Training on MI will be in accordance with an MI guide that covers key points for MI as well as examples and key insights to assessing patient risk, risk reduction counselling and inspiring behaviour change [16]. Participants in hospitals randomised to usual care will receive the normal care obtainable in the HIV treatment hospitals. This typically involves monthly or bi-monthly scheduled hospital visit for medical examination, prescription refill and adherence counselling, bi-yearly VL assessment, and yearly CD4^+^ count analysis.

In addition to the usual care, participants in the intervention hospitals will receive MI at baseline and following initiation of ART, they will receive a gift voucher of US$5.6 when VL < 20 copies/mL at 12 weeks, a gift voucher of US$2.8 if the VL remains suppressed for the next 3 months, and the next 6 months, and finally a gift voucher of US$5.6 if the VL remains < 50 copies/mL at 1 year. All incentives will be conditional not only on patients meeting their VL target but attending for MI. Those with VL higher than the thresholds will not receive the incentive. The potential maximum cumulative financial incentive is US$16.8 if viral suppression is sustained for 12 months. The patient will have the liberty to withdraw from the scheme at any time point. Routine hospital data will be collected and outcomes will be assessed by changes in HIV VL and CD4+ count from baseline, at 12 months from enrolment and at 24 months to establish whether any benefit is seen from the intervention could be sustained when financial incentives cease. Each patient in the study will be assigned to a study nurse working in the HIV treatment hospital and they will be tracked with their mobile phone numbers.

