### Randomisation

We will stratify each cluster unit (HIV treatment hospital) according to the type of clinic (secondary or tertiary). We will randomly allocate each HIV treatment hospital in each stratum into the intervention arm or the control arm. The randomisation schedule will be done using Research Randomiser, a web-based computer random-number generator [19]. The randomisation schedule will be carried out by an independent person who is not part of the research team.

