## Trial status

This is protocol version 1.0 as at 23 August 2018. Recruitment is planned to begin on 1 December 2018 and completed on 28 February 2019.

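### Hospital staff recruit adolescents who must be willing to restart therapy, and no described step identifies them before the hospital's arm is disclosed, so the arms may differ from the start

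*Protocol article*

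**What the plan says.** All references are to the protocol article.

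- **Unit and assignment.** Under Trial sites selection, hospitals are matched by type and "the paired units will be randomly assigned to intervention or control". Under Randomisation, "The randomisation schedule will be carried out by an independent person who is not part of the research team". No date for randomisation is given.
- **Who recruits.** Under Recruitment and retention: "Eligible adolescents will be recruited by the study personnel in the trial site (e.g. trial physician or nurse". The same section adds that "Each study participant will be assigned to a study nurse working in the HIV treatment hospital".
- **Who can enter.** Under Participants, the adolescent must be "willing to restart therapy and sign a written informed consent"; Table 1 repeats the willingness criterion. Another criterion is poor adherence, defined as "< 95% adherence rate assessed through pill count or self-report".
- **What differs between hospitals.** The Intervention section applies the Incentive Scheme to whole hospitals. It adds that "participants in the intervention hospitals will receive MI at baseline" and that vouchers can total US$16.8. Control hospitals give usual care.
- **Numbers and timing.** The Sample size section asks each hospital for 23 participants. Trial status gives a three-month window: "Recruitment is planned to begin on 1 December 2018 and completed on 28 February 2019".
- **Analysis.** Statistical analysis and Table 3 specify intention to treat, a chi-square or Fisher's exact test for the primary outcome, and a descriptive comparison of baseline characteristics.

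**The concern.** Randomising hospitals makes the hospitals comparable on average. It makes the participants comparable only if the route from eligible adolescent to enrolled participant is the same in both arms. When the arm is known at recruitment, two things can break that.

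- **Staff choice.** A recruiter who knows the arm may approach different adolescents, or apply a judgement-based criterion such as self-reported adherence differently.
- **Adolescents' own response.** Willingness to restart therapy is an entry criterion, and an offer of vouchers can alter it. The incentive may then act on who enters the trial as well as on what happens afterwards.

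Motivation plausibly predicts viral suppression, so a difference between arms in who enters would appear as a treatment effect, or would hide one. Intention to treat keeps enrolled participants in their arm but does not change who was enrolled. An unadjusted test makes no allowance for a different case mix. The Study rationale section lists selection bias among the weaknesses of the earlier non-randomised design, so this is a threat the trial itself sets out to avoid.

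**Working it through.** **Step 1: the order of events.** For each safeguard that would prevent the problem, the visible text gives the following.

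| Safeguard | What the article gives |
|---|---|
| Participants identified before allocation is released | Not described; assignment appears under site selection |
| Recruiters outside the hospital, or masked to arm | Recruiters are personnel at the site; no masking described |
| All eligible patients listed or approached in a set order | Not described |
| Independent person | Runs the hospital randomisation only |

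A hospital that is to give motivational interviewing at baseline and then issue vouchers has to be told its arm. Unless all its participants are enrolled first, its recruiters will very probably know it.

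**Step 2: the plan's own figures, as a yardstick.** Inputs from Sample size: difference 12 points, SD 24 points, 80% power, two-sided 0.05, ICC 0.047, six hospitals per arm.

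- Before clustering: 2 × (1.96 + 0.84)² × (24/12)² ≈ 63 per arm. This agrees with the plan.
- With six hospitals fixed: 63 × (1 − 0.047) / (6 − 63 × 0.047) = 60.04 / 3.04 = 19.8, so 20 per hospital and 120 per arm. This agrees.
- Attrition: 120 + 6 × 3 = 138 per arm, or 23 per hospital. This agrees.

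The yardstick is therefore the 12-point target.

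**Step 3: illustration of size.** With no treatment effect, the spurious difference equals the difference between arms in the share of highly motivated participants, multiplied by the suppression gap between more and less motivated participants. Neither input is in the article; both ranges are assumptions.

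| Share differs by | Gap 20 points | Gap 30 points | Gap 40 points |
|---|---|---|---|
| 10 points | 2 | 3 | 4 |
| 20 points | 4 | 6 | 8 |
| 30 points | 6 | 9 | 12 |

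The range of 2 to 12 points is 17% to 100% of the target. If recruitment is the same in both arms the value is zero, and the sign can go either way.

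**Step 4: effect on the test, for one cell.** Take a spurious 6 points, 23 per hospital and control suppression of 40% to 50% (assumed).

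- Design effect: 1 + 22 × 0.047 = 2.034. Effective size per arm: 138 / 2.034 = 67.8.
- At 50% v 56%: SE = √[(0.25 + 0.2464) / 67.8] = 0.0856, and 0.06 / 0.0856 = 0.70.
- A cluster-adjusted test (normal approximation) rejects in about 11% of trials instead of 5%.
- The planned unadjusted test rejects in about 27%, against about 17% with no spurious difference. The excess already present at zero comes from ignoring clustering, which is a separate matter.

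Recruiting more participants per hospital does not remove a bias of this kind.

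**The case against.** The strongest reply is that the article nowhere says recruiters know the arm, does not say who takes consent, and gives no order for enrolment and release of allocation. Baseline motivational interviewing is compatible with consent first and allocation second, and it is given by an adherence counsellor, whereas the recruiters named as examples are a physician or nurse. Fig. 1, whose title covers the enrolment schedule, and Additional file 1 are not available here and might settle the order. This stands as a limit: knowledge of the arm is an inference. It is a strong one, because recruitment is by site personnel for a scheme that cannot be hidden from the site.

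A reader might also infer that staff have wide freedom to pick 23 adolescents. The article does not support that. The criteria are narrow, and the Discussion expects slow enrolment at hospitals with few patients while also describing the chosen hospitals as having good client load. The size of the pool is unknown. A small pool limits staff choice but does not stop vouchers from changing who agrees.

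Finally, a reader might take 6 points, half the target, as the expected bias. It is one cell of an illustration with assumed inputs, and the documents support neither that size nor a direction.

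That cluster trials of this kind cannot be blinded is true but does not answer the point, which concerns the order of identification and disclosure.

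**Conclusion.** The concern holds as a design weakness. As described, site personnel recruit under a motivation-dependent criterion for a hospital-wide scheme, with no step that fixes the candidates before the arm is disclosed. The independent randomiser protects the hospital sequence but not the selection of individuals, and the planned analysis cannot repair differential recruitment afterwards.

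The conclusion rests on one inference, that allocation is known at the hospital while it recruits. It would fail if every participant were enrolled before release, which the visible text does not say. The figures of 2 to 12 points show only that plausible inputs could matter against a 12-point target; they should carry no weight as an estimate.

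**What to change.** State the sequence in the protocol:

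1. Before the independent person releases any allocation, each hospital draws a list of eligible adolescents from its clinic register and freezes it. All 12 lists should be frozen first, because disclosing one hospital of a matched pair discloses the other.
2. Adolescents are invited from the frozen list in random order. Willingness is recorded at invitation, so refusals are counted.
3. Eligible, invited, consenting and enrolled numbers are reported by arm and hospital.
4. Where this is feasible without delaying participants' care, consent and baseline sampling are also completed before release, using information that does not reveal the arm.

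The cost is listing work at 12 hospitals and, if step 4 is used, a somewhat later start of the scheme. Holding allocation until every hospital in a pair or stratum has consented its 23 would protect better. It should not be made an absolute requirement, because slow sites could keep adolescents who are off therapy waiting. The frozen list limits recruiter choice but does not fully remove differential consent; the counts by arm make what remains visible.

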### Trial subject safety

The major risk envisaged in this trial will be exposure of the data of study participants. In order to mitigate this risk, patients’ data will be treated with confidentiality. All personal data collection and processing will be carried out according to European Union (EU) and national legislation. Personal data collected are those necessary to establish the primary and secondary study outcomes. Unique identifiers and a password-protected database will be used to protect the personal information of the study participant. We will keep a written document with detailed information of the origin of all used human samples. All the study partners in the different study sites will receive training on procedures for handling pseudonymised data during study briefing/training. Training will be based on the principle of handling personal data elucidated in the ‘Article 29 Data Protection Working Party’. To ensure the protection of personal data, the principal investigator (PI) (including data analyst) will receive only key-coded data.

### Management of incidental findings and data monitoring

There is a chance of anticipatable incidental findings due to the increased number of laboratory testing (especially for those in the intervention arm) and closer monitoring. These anticipatable incidental findings include early detection of the following:Clinical failure: this is the presence of new or recurrent clinical event indicating severe immunodeficiency (WHO clinical stage 4 conditions) following 6 months of effective treatmentImmunological failure: this represents a CD4+ cell count fall to or below pre-treatment baseline value or persistent CD4+ levels below 100 cells/mm^3^ or 50% decline from on-therapy CD4+ cell count peak levelVirologic failure: this is the persistently detectable VL exceeding 1000 copies/mL (that is, two consecutive VL measurements within a 3-month interval, with adherence support between measurements) after at least 6 months of using antiretroviral drugs

Any such anticipatable incidental findings will be disclosed to the participants and their parents/legal guardians (for those less than 18 years). Management of these anticipatable incidental findings will be in accordance to the National Guidelines for HIV Prevention, Treatment and Care. This entails the following: providing adherence support and treating opportunistic infections in any suspected case of treatment failure; reassessing VL and.

CD4+ improvement after 3 months; and changing to second-line therapy in case of no improvement (i.e. VL > 1000 copies/mL).

Any study-related adverse events (AEs) will be documented and reported to the Steering Committee/Data and Safety Monitoring Board. In the case of a serious adverse event (SAE), it will be reported to the Nnamdi Azikiwe University Ethics Committee within 14 days of the PI becoming aware of the event. SAE is defined as an untoward occurrence that (1) results in death; (2) is life-threatening; (3) requires hospitalisation or prolongation of existing hospitalisation; (4) results in persistent or significant disability or incapacity; (5) consists of a congenital abnormality or birth defect; and (6) is otherwise considered medically significant by the investigator.

Conditions in which expedited reporting will not apply include hospitalisation for (1) treatment which was pre-planned, or for a pre-existing condition not associated with any deterioration in condition and (2) treatment on an emergency, outpatient basis for an event not fulfilling any of the definitions of serious as given above and not resulting in hospital admission. Patients will be asked if any adverse events have occurred when they attend for any trial-related visits.

### Trial management

The Steering Committee will also serve as the Data and Safety Monitoring Board (DSMB). This committee is composed of two of the authors and three external, independent experts in HIV care, pharmacology and pharmacy (Appendix). The Steering Committee/DSMB will provide overall supervision of the trial. Specifically, the committee will: (1) review and evaluate the accumulated study data every 6 months for patient safety and (2) study the conduct and progress of the trial and make appropriate recommendation to the trial team.

### Trial monitoring

A standard operating procedure defining the responsibilities, processes and deadlines for the monitoring of the ARA trial as well as a monitoring manual will be prepared. This is to ensure uniform monitoring of all the sites in the trial.

### Clinical trial registration

This trial is registered in the WHO International Clinical Trials Registry through the WHO International Registry Network (https://pactr.samrc.ac.za/: PACTR201806003040425).

## Discussion

The findings of this proposed trial should provide evidence on the feasibility of applying conditional economic incentives combined with MI to improve retention and adherence to antiretroviral therapy of adolescents living with HIV in Nigeria and possibly in other sub-Saharan African countries.

We anticipate that enrolment of adolescents with HIV might be slow especially in HIV treatment hospitals with a low patient load. However, we included 12 HIV treatment hospitals that offer comprehensive HIV counselling and antiretroviral treatment services with good client load (including adolescents).

## Trial status

This is protocol version 1.0 as at 23 August 2018. Recruitment is planned to begin on 1 December 2018 and completed on 28 February 2019.

## Abbreviations

AIDS: Acquired immunodeficiency syndrome
ART: Antiretroviral therapy
CEI: Conditional economic incentive
HIV: Human immunodeficiency virus
ICER: Incremental cost-effectiveness ratio
IDI: In-depth interview`
MCH: Maternal and child health
MI: Motivational interviewing
NACA: National Agency for the Control of AIDS
NGN: Nigerian Naira
RCT: Randomised controlled trial
SPSS: Statistical Package for the Social Sciences
SSA: Sub-Saharan Africa
SURE-P: The Subsidy Reinvestment and Empowerment Programme
UCSF: The University of California, San Francisco
VL: Viral load
WHO: World Health Organisation
